## Abstract

**Background:**

Intravitreal injections (IVI) of anti-vascular endothelial growth factor (anti-VEGF) now improve or stabilize visual acuity in a number of previously untreatable eye diseases, of which the main are age-related macular degeneration, retinal vein occlusion and diabetic macular edema. Most patients require multiple injections over lengthy periods of time and the prevalence of treatable conditions is increasing. Anti-VEGF IVI normally administered by physicians, therefore represent a considerable workload on ophthalmologic clinics and will continue to do so in the near future. Nurse-administered IVI may relieve this workload, but the safety, cost and patient satisfaction of such an extended role for nurses in ophthalmologic clinics has not earlier been investigated. To investigate these outcomes following independent anti-VEGF IVI by trained nurses, a noninferiority randomized controlled trial is being conducted.

**Methods/Design:**

Patients eligible for anti-VEGF treatment, minimum 304, are recruited and randomized to IVI administration by either trained nurses or physicians. The primary outcome is safety, measured by difference in mean change in visual acuity between the two groups during an observation period of 12 months. Secondary outcomes are incidence of ocular adverse events, cost per patient and patient satisfaction.

**Discussion:**

This study protocol describes the design of the first randomized controlled trial of nurse-administered IVI of anti-VEGF. The study is designed to examine safety, cost and patient satisfaction during 12 months follow-up.

**Trial registration:**

ClinicalTrials.gov NCT02359149. Registered February 4, 2015.

**Electronic supplementary material:**

The online version of this article (doi:10.1186/s12886-016-0348-4) contains supplementary material, which is available to authorized users.

## Background

Intravitreal injections (IVI) of anti-vascular endothelial growth factor (anti-VEGF) improve or stabilize visual acuity in a number of previously untreatable eye diseases, of which the main are age-related macular degeneration (AMD), retinal vein occlusion (RVO) and diabetic macular edema (DME) [1–3]. Due to its potent antiangiogenic effects, the number of IVI of anti-VEGF has risen considerably since the treatment was first introduced a decade ago [4, 5]. Elderly people with AMD make up the largest group of patients receiving IVI and the prevalence of the disease increases with age. In the UK 3.5 % of the population of 75 years or older were visually impaired due to AMD [6]. In 2010, more than two million people were blind and six million people were visually impaired due to macular diseases globally [7]. Improved diagnostics as well as increased prevalence of treatable conditions will probably cause a continued rise of IVI in the future. IVI are normally administered by physicians in ophthalmologic out-patient clinics and are given with intervals of 4–16 weeks either as monthly injections, injections when needed (pro re nata) or injections with gradually extended intervals (treat and extend) [8, 9]. Irrespective of the treatment strategy chosen, most patients require sequential injections during several years for their condition to stabilize. Hence, IVI of anti-VEGF represent a considerable workload on physicians in ophthalmologic clinics and is expected to continue to do so. This is a real challenge today and in the future, since the population over age 60 are growing more than twice as fast as the number of ophthalmologists [10].

Extended roles for nurses are increasingly implemented in several medical fields, and in ophthalmology nurse-administered IVI of anti-VEGF may replace physician-administered IVI. Data on nurse-administered IVI is limited so far, but there are indications that it may be safe and acceptable to patients. An observational study from the UK reported a complication rate comparable to studies in which IVI were administered by physicians [11] and other studies have reported acceptable patient satisfaction following nurse-administered IVI [12–14]. However, these outcomes have to the best of our knowledge not earlier been investigated in randomized controlled trials (RCT) and an economic evaluation of a nurse-administered IVI clinic has not earlier been reported. To this end, the present protocol describes a noninferiority RCT with the objective to investigate safety, cost and patient satisfaction following nurse-administered IVI during 12-months follow-up.

## Methods

### Study design

The study is a prospective, randomized noninferiority trial with two treatment arms; IVI performed by nurses and IVI performed by physicians. Treatment by physicians is considered the reference group and standard care to which treatment performed by nurses will be compared. The flow chart of the study is presented in Fig. 1.

**Fig. 1 Fig1:**
[figure not shown]
Flowchart. Overview of the enrollment and follow-up of study participants

### Objectives

The primary objective is to evaluate the safety of nurse-administered IVI of anti-VEGF compared with physician-administered IVI.

The secondary objectives are:to evaluate cost of nurse-administered IVI of anti-VEGF compared with standard careto evaluate patient satisfaction of nurse-administered IVI of anti-VEGF compared with standard care

For the primary objective the evaluation will be performed using a noninferiority test, to test whether the nurses are treating the patients equally safe or better than the reference group, i.e physicians. More specifically, the null (H_0_) and alternative (H_A_) hypotheses are:$$ {\mathrm{H}}_0:\ {\upmu}_{\mathrm{NURSES}}\hbox{--}\ {\upmu}_{\mathrm{PHYSICIANS}}\le -{\updelta}_{\mathrm{L}}\kern0.37em \mathrm{and}\;{\mathrm{H}}_{\mathrm{A}}:\ {\upmu}_{\mathrm{NURSES}}\hbox{--}\ {\upmu}_{\mathrm{PHYSICIANS}}> - {\updelta}_{\mathrm{L}}, $$

where μ _i_ is the mean change in visual acuity from first visit (baseline) to last visit 12 months later in group i, and δ_L_ is “the noninferiority margin”, which is the maximum clinically acceptable difference in change, for treatment by nurses to be considered noninferior to the reference treatment, δ_L_ >0

### Setting

The trial is performed in the IVI clinic of the Department of Ophthalmology, St. Olavs Hospital, Trondheim University Hospital in Norway during 01.03.15-31.12.16. The IVI clinic, organized as an independent out-patient clinic, performs ~ 3000 IVI annually and serves a population of ~ 300.000 individuals in the Central Norway Health Region.

Patients are remitted to the IVI clinic by ophthalmologists working at 10 different eye centers in the region and from ophthalmologists at the Department of Ophthalmology, responsible for the diagnostic and therapeutic decisions. At the IVI clinic a secretary administers patient appointments, receive user charges and answer phone calls. Preparing the patients for IVI is performed by a nurse (Additional file 1). In standard care, a physician is responsible for performing the IVI according to the list of patients, approximately 22 IVI daily (Additional file 2). A senior consultant is available at the clinic in case medical questions need to be discussed.

### Intervention

The intervention in the present study consists of replacing the physician administering the IVI, by a nurse (Additional file 2). Administration of IVI includes several skills and responsibility: assessment of whether there are any contraindications for treatment, performing the sterile IVI procedure, informing the patient, planning the next session and documentation in patient records. The preparation for IVI by a nurse (Additional file 1) and the possibility to seek medical advice from a senior consultant remains equal to standard care.

### Training program

A training program for administration of IVI for nurses was developed and implemented at the Department of Ophthalmology during the year prior to the start of the RCT. Six nurses took part in the training program which aimed at enabling nurses to perform IVI independently, as safe and within equal time frame as the physicians.

The program included two interactive courses regarding eye infections and documentation in patient records. Furthermore, it included a wetlab with individual training of a safe injection technique on porcine eyes; placing the injection 3.5 mm posterior to the limbus in any quadrant between the horizontal and vertical muscles. This was followed by graded exposure of the procedure in the injection room and finally performing IVI individually on patients under the supervision of a physician. The training program was divided into steps with increasing difficulty and the participating nurses decided themselves when they were ready to move to the next step. The nurses had to perform 100 independent IVI before final certification. The final achieved competence was evaluated by an unbiased senior consultant via observation of the nurse performing three independent IVI. If these were performed in a satisfactory manner, the nurse was certified to administer IVI individually.

### Trial recruitment

All patients with AMD, RVO or DME that are eligible for anti-VEGF IVI and able to give an informed consent are invited to participate. Both newly referred patients during 01.03.15–01.01.16 as well as patients that are already receiving anti-VEGF IVI fulfil the inclusion criteria.

Patients with ocular pathology eligible for anti-VEGF IVI other than the abovementioned conditions and inability to provide an informed consent do not fulfil the inclusion criteria and are excluded.

Information about the study will be given either face-to-face in the department or via a phone call and will also be handed out in writing. The patients will receive trial information at least 24 h before being asked to give an informed consent. If the patient agrees to enter the trial, written informed consent will be obtained. Consent forms will be stored in a locked safe to which only study management has access. Patients who do not consent to the trial will be treated according to standard care.

### Randomization and blinding

Patients are randomly assigned to receive treatment by nurse or physician in a 1:1 ratio, using a web-based algorithm. The randomization is stratified by diagnosis (AMD, RVO and DME) and by number of treatments (first treatment vs treated before). The reason for choice of stratification is that there is an expected difference in change in mean visual acuity during the observation period in these groups. Only one eye per patient is included in the study. If both eyes are eligible, the eye with the better visual acuity is included.

The study is single-blinded, i.e. patients are blinded to intervention group. Patients are not told to which group they have been randomized, and both nurses and physicians will wear white hospital clothes but no nametags telling their profession during the procedure. Furthermore, when the patient enters the injection room the personnel will present themselves by first name only.

### Outcomes

Primary outcome is the difference in mean change in visual acuity between the two groups during the study period of 12 months (measure 1).

Secondary outcomes are:incidence of ocular adverse events needing treatment (measure 2)cost per patient (measure 3)mean patient satisfaction score (measure 4)

### Measures

*Visual acuity* is measured with the Early Treatment Diabetic Retinopathy Study (ETDRS) chart using a standardized testing protocol at a starting test distance of 2 m [4, 5]. The visual acuity is measured as number of letters read at the ETDRS chart. Each line of the chart has five letters of same size in each row. The letters of the following rows gradually become smaller, with a distance of 0,1 logMAR. This interval scale is considered a continuous variable, and the number of letters read is counted [15]. The mean number of letters scored is considered a precise measure for evaluating whether the intervention shifts the visual acuity compared to standard care.

The test is carried out under uniform conditions by a physician, orthoptist or an optician. Before testing, the refraction is corrected following a standard protocol [15], i.e. the vision tested being the best corrected visual acuity.2.*Ocular adverse events*. Number of ocular adverse events in the population receiving IVI at the Department of Ophthalmology is recorded during the whole study period, from the first study visit to the last follow-up visit of the study. The ocular adverse events will be noted in patient record and on a dedicated study form. Only ocular adverse events needing treatment are being recorded; retinal detachment, retinal tears, endophthalmitis, uveitis, lens damage and intraocular hemorrhages.3.*Cost per patient*. Cost data will be collected in order to take a hospital perspective, a health care perspective and a societal perspective.

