### Data collection

At the first visit, background information for the economic evaluations is collected (Additional file 4). A physician, orthoptist or optician is asking these questions before refractioning the study eye and measuring the best corrected visual acuity. The study participant then goes to the injection room. After the IVI, the participant is asked to answer the patient satisfaction questionnaire by a secretary (Additional file 5). Each study participant has an individual study booklet marked with study number and patient initials. The booklet follows the patient during the visit in the department and is otherwise kept in a locked room.

In the following visits the study participant will be asked follow-up questions regarding use of health care service (Additional file 4). The questions are asked by the nurse or physician performing the IVI.

The last visit of the 12 month period is performed similar to the baseline registration (Additional file 4). The time window for the final test is 12 ± 2 months.

The nurse or physician performing the IVI, will fill in a daily report including the number of patients and eyes treated and number of questions asked a senior consultant (Additional file 3).

Researchers will continually examine the study forms in the booklets for missing data. Missing data will be sought collected via phone calls.

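### Only patients are blinded: nothing requires the person who scores the primary acuity test to be unaware of the arm or to be someone other than that patient's injector

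*Protocol article*

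**What the plan says.** Under Randomization and blinding, the article states: "The study is single-blinded, i.e. patients are blinded to intervention group". The masking measures that follow (clothing, no nametags, introduction by first name) are all directed at the patient.

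Under Outcomes: "Primary outcome is the difference in mean change in visual acuity between the two groups during the study period of 12 months". Under Measures, the scoring is described thus: "The visual acuity is measured as number of letters read at the ETDRS chart". On who does it: "The test is carried out under uniform conditions by a physician, orthoptist or an optician". Refraction comes first: "Before testing, the refraction is corrected following a standard protocol".

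Under Data collection, the same staff groups interview the patient at the first visit: "A physician, orthoptist or optician is asking these questions before refractioning the study eye and measuring the best corrected visual acuity". The final visit follows the baseline pattern. On paperwork: "Each study participant has an individual study booklet marked with study number and patient initials", and "The booklet follows the patient during the visit in the department and is otherwise kept in a locked room". At the visits in between, the injecting nurse or physician asks the questions on use of health care.

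No section says that the acuity tester is masked or must differ from the injector.

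**The concern.** Best corrected acuity depends partly on the examiner, through the refraction, the encouragement given and the count of letters. Physicians form the reference arm and are also among the permitted testers, and the trial runs in a single clinic. As written, the plan would allow a tester to know who had been injecting a patient, or to have given the injections personally.

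The noninferiority margin is 3 letters, less than one five-letter chart line. A small difference in scoring between arms would therefore be large relative to the margin, and could not be separated from a treatment effect afterwards. The article sets the blinding level explicitly and defines it as patients only, so this is a stated design choice and not a detail left to a fuller document.

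**Working it through.** **Inputs from the article (Sample size; Randomization and blinding).** Margin 3 letters, SD of change 10 letters, true difference 0, significance level 0.05, power 80%, 140 completers per arm, 1:1 allocation.

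**Step 1: reproduce the plan's figure.** n per arm = 2 × SD² × (z_alpha + z_power)² / margin² = 2 × 100 × (1.645 + 0.842)² / 9 = 137.4, so 138. This agrees with the stated 140 when 0.05 is taken as one-sided. At one-sided 0.025 the formula gives 175, which does not agree. The checks below therefore use one-sided 0.05.

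**Step 2: standard error.** SE = 10 × √(2/140) = 1.195 letters. Power at a true difference of 0 is Φ(3/1.195 − 1.645) = 80.7% (80.5% by noncentral t).

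**Step 3: define the bias.** Let b be the average scoring shift at the final test in the nurse arm minus that in the physician arm. Leniency applied equally to both arms gives b = 0 and cancels. At the first visit acuity is measured before the injection, so the exposure is mainly at the 12-month test. The article gives no value for b; the values below are assumptions.

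**Step 4: effect of b.**

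- Bias favouring nurses, true difference −3: false noninferiority = 1 − Φ(1.645 − b/SE).
- Bias against nurses, true difference 0: power = Φ((3 − b)/SE − 1.645).

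| Assumed size of b (letters) | False noninferiority if b favours nurses | Power if b is against nurses |
|---|---|---|
| 0 | 5.0% | 80.7% |
| 0.5 | 11.0% | 67.3% |
| 1 | 21.0% | 51.1% |
| 1.5 | 34.8% | 34.8% |
| 2 | 51.1% | 21.0% |

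For b = 1, for example: b/SE = 1/1.195 = 0.837, and 1 − Φ(1.645 − 0.837) = 1 − Φ(0.808) = 21.0%. In the other direction, (3 − 1)/1.195 − 1.645 = 0.028 and Φ(0.028) = 51.1%.

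**Step 5: does masking change the sample size?** No. It enters none of the inputs, so 140 completers and 152 enrolled per arm stand.

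**The case against.** Three stronger readings are tempting, and the article supports none of them.

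*That testers know the arm through the booklet.* The booklet is described as carrying a study number and initials, with no mention of arm or injector. The injector asks the follow-up questions, but the article does not say that the answer sheet shows a name or profession; the form itself is in an additional file that is not shown. The daily report completed by the injector is not described as part of the booklet. The acuity test also precedes the injection room, so the tester need not meet that day's injector. Unmasking is possible, not established.

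*That the bias runs toward noninferiority.* An expectation of no difference would pull a real deficit toward zero, and the department did train its own nurses. But physician testers belong to the reference profession and could as easily score against nurses, which would cost power and not produce a false claim. The direction is open.

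*That the percentages are expected harm.* They show how sensitive the test is to assumed shifts. The document offers no estimate of the shift.

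The stated safeguards also deserve credit: a standardized chart protocol, standard refraction, uniform conditions, a letter count, and a blinded patient doing the reading. They narrow the room for examiner influence.

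All of this stands. It does not remove the point, because none of these safeguards keeps the tester unaware of the arm or separates the tester from the injector. At the last visit patients are asked whom they believe treated them; no matching check is described for testers.

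**Conclusion.** The point holds as a weakness in the stated design, not as a demonstrated bias. Blinding is confined to patients, a physician may score the primary outcome, and nothing keeps the tester unaware of the arm or distinct from that patient's injector. Under the plan's own assumptions (SD 10, 140 per arm, one-sided 5%), a differential of only 0.5 to 1 letter would matter: false noninferiority at the margin of about 11-21% in place of 5%, or power of about 67-51% in place of 81%, depending on its sign. Both the size and the sign of the differential are assumptions. The change is worth making because it is cheap and protects the primary comparison in either direction.

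**What to change.** For the 12-month tests still to be done:

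- Assign the acuity test to the orthoptists and opticians already used, or to a physician who has not injected that patient and is not told the arm. Not having injected is not enough by itself to make a tester masked.
- Keep any sheet that identifies the injector away from the tester.
- Record on the test form whether the tester knew the arm.

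In the protocol and report, describe as assessor-masked only the tests actually done that way. Recruitment began in March 2015 and the final-visit window opens at 12 − 2 = 10 months, so final tests could have begun by January 2016. Relabelling the whole trial could therefore be inaccurate. If testers are already masked in practice, the protocol should say so.

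Report a sensitivity analysis by tester masking status as supportive only. It conditions on a factor that arises after randomization and may differ by arm, and it loses precision by using fewer than the planned 140 per arm. It does not repair the primary analysis.

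The cost is less flexible rostering among existing testers and some rearrangement of paperwork. No new category of staff is needed and the sample size is unchanged. The article does not give the number of orthoptists and opticians, so the clinic must confirm that they can cover the remaining visits.

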#### Patient costs

Travel costs will be calculated based on information on travel time and bringing a companion.4.*Patient satisfaction*. Previously validated patient satisfaction instruments were found too comprehensive and not suitable to assess the IVI treatment in the injection room setting. A short and simple study-specific patient satisfaction questionnaire was therefore developed in accordance with guidelines for measuring the quality of health services [16]. The questionnaire was validated for reliability and feasibility in a pilot study of 10 patients. After this first pilot test, some modifications were made to the questionnaire before a second pilot test was carried out and validated. We found the best alternative for the patients with blurred vision following treatment to be a five-point grading scale and only a few questions read out load. Only two aspects of the treatment is tested; the general impression of the treatment and the confidence during the treatment in the injection room (Additional file 5). If the patient is not giving the maximum score of satisfaction, an open-ended question will be asked for recommendations of how to improve the comfort and well-being during the visit. At the last visit, the patients additionally will be asked if they think they are treated by a nurse or by a physician.

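### Adverse-event recording ends at the last follow-up visit with no period after the final injection, so complications of an injection given at that visit may go uncounted

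*Protocol article*

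**What the plan says.** **The recording window.** Under Measures (item 2), the events counted are those in "Number of ocular adverse events in the population receiving IVI at the Department of Ophthalmology". Recording covers the entire study period, "from the first study visit to the last follow-up visit of the study". On the source of the data: "The ocular adverse events will be noted in patient record and on a dedicated study form". No time after an injection is added to the closing point.

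**The order of a visit.** Data collection puts the acuity test first at the baseline visit. Then: "The study participant then goes to the injection room". Then: "After the IVI, the participant is asked to answer the patient satisfaction questionnaire by a secretary".

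**The last visit.** The same section says: "The last visit of the 12 month period is performed similar to the baseline registration". The patient satisfaction text, printed under Patient costs, adds: "At the last visit, the patients additionally will be asked if they think they are treated by a nurse or by a physician".

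**The role of the outcome.** Under Outcomes, the incidence of these events is a secondary outcome. The Discussion says that the trial is not sized for it because complications are very rare, but also that examining adverse events is important.

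**The concern.** The primary objective is safety, and the adverse-event outcome is the only one that counts complications directly. The listed events include endophthalmitis, uveitis and retinal detachment, which may show only after the patient has gone home. If an allocated injection is given at the visit that closes the window, a complication appearing later is outside the stated count. It cannot show in the primary outcome either, because in the described order the final acuity test comes before the injection.

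The article states a start and an end for recording. The point is therefore about a rule as written, not about detail left to a fuller document.

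**Working it through.** **1. Is an injection given at the last visit?** The baseline sequence is acuity test, injection room, questionnaire after the injection. The last visit is described as similar, and a question about who is treating the patient is added at that visit. The questionnaire concerns treatment in the injection room. Together these imply that an injection is normal at the last visit. No sentence says so for every patient.

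**2. Whose last visit closes the window?**
- *Per patient:* Measures speaks of the whole study period, and Outcomes gives the study period as 12 months. Setting has the trial running from 01.03.15 to 31.12.16, about 22 months, so a 12-month period must be each patient's own.
- *Study-wide:* the closing visit is described as that of the study, and the population is described at clinic level.

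The first reading is better supported; the second is not excluded.

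**3. Number of completers.** Sample size gives 140 per arm. With margin 3, SD 10, true difference 0, power 80% and a one-sided 0.05 level (the article does not state the side), n = 2 × (10/3)² × (1.645 + 0.842)² = 137.4, so 138 per arm. This agrees with 140 to within 2 patients. Completers: 2 × 140 = 280.

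**4. Per-patient window.** At most one final-visit injection per completer lacks follow-up, so up to 280 injections. To illustrate the share, assume fixed intervals within the 4–16 weeks given in Background and an injection at both end visits. Injections per patient = 52/interval + 1.

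| Interval (weeks) | Injections | Share that is the last one |
|---|---|---|
| 4 | 14.0 | 1/14.0 = 7% |
| 8 | 7.5 | 1/7.5 = 13% |
| 12 | 5.3 | 1/5.3 = 19% |
| 16 | 4.25 | 1/4.25 = 24% |

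**5. Study-wide window.** Trial status gives recruitment from 1 March 2015 to December 2015; taken to 31 December this is 306 days, or 306/7 = 43.7 weeks. Assume uniform recruitment, a last visit at exactly 12 months and a risk period of 4–6 weeks (the article gives none). The completers whose risk period runs past the end of recording are then:
- 4 weeks: 4/43.7 = 9.2%, and 0.092 × 280 ≈ 26 patients
- 6 weeks: 6/43.7 = 13.7%, and 0.137 × 280 ≈ 38 patients

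**6. Expected events lost.** The article gives no event rate. Assuming 0.02–0.1% per injection:
- 280 uncovered injections: 280 × 0.0002 = 0.06 to 280 × 0.001 = 0.28 events
- 38 uncovered injections at the upper rate: 38 × 0.001 = 0.04 events

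**The case against.** The strongest case against is that the window is a calendar window for the clinic. For an individual's final visit the article uses other wording, tied to the 12-month period. On that reading a patient enrolled in March 2015 stays under observation until the turn of 2016/17, and only late recruits are exposed to the gap. This stands as a possible reading, but it does not close the gap. It also raises a second question: early completers would be observed well beyond 12 months, and the article does not say who injects them then.

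A reader might infer three stronger statements, none of which the article supports:
- *Every completer has one unobserved injection.* The last-visit injection is inferred, the sentence on similarity cites the registration form, and Background allows as-needed and extended intervals. The figure of 280 is an upper bound. Complications apparent during the visit would still be recorded.
- *The per-injection rate is understated by 7–24%.* Outcomes defines no per-injection denominator, and the intervals come from a description of general practice, not from this trial's schedule. The range only illustrates a share of injections.
- *The comparison of nurses with physicians is biased.* The same cut-off applies to both arms, and nothing in the article shows a differential loss.

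It is also fair that an acuity endpoint at a fixed time never captures later harm, and that events noted in the patient record may still be known to the clinic. Even so, the stated rule would not count them.

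**Conclusion.** The point holds in limited form. As written, recording of ocular adverse events stops at a last follow-up visit with no allowance after the final injection, and an allocated injection is normally to be expected at that visit. The better-supported per-patient reading leaves up to about 280 final injections without stated follow-up. The study-wide reading leaves roughly 26–38, under the assumptions of uniform recruitment, a last visit at exactly 12 months and a 4–6 week risk period.

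The effect is to lower recorded incidence in both arms on a secondary outcome for which the trial is not sized. At the assumed event rates the expected loss is below one event. The primary non-inferiority test is unaffected. The change is still worth making: it is cheap, and with so few events expected, a single uncounted one would alter the safety account.

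**What to change.** In Measures, item 2, replace the closing point. State that recording runs for each patient from the first study injection to a fixed period (for example 30 days) after that patient's last study injection. Ascertain events from the patient record, already named there, and from the hospital administrative register, already used under Other hospital costs. A fixed period is preferable to one tied to the next visit, which at the intervals in Background could be up to 16 weeks away.

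For each event, record which injection it followed. At a 4-week interval the next injection could fall on day 28, inside a 30-day window.

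If the window is not extended and a per-injection rate is reported, leave final-visit injections without follow-up out of the denominator.

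The cost is one sentence, a record check for about 280 completers in sources the trial already consults, and about one month's delay in closing data for the last patients.
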